## Abstract

**Background:**

Despite the success of HMG-CoA reductase inhibitor (statin) therapy in reducing atherosclerotic cardiovascular events, a residual risk for cardiovascular events in patients with coronary artery disease (CAD) remains. Long-chain n-3 polyunsaturated fatty acids (LC n-3 PUFAs), especially eicosapentaenoic acid (EPA) and docosahexaenoic acid (DHA), are promising anti-atherosclerosis agents that might reduce the residual CAD risk. Non-contrast T1-weighted imaging (T1WI) with cardiac magnetic resonance (CMR) less invasively identifies high-risk coronary plaques as high-intensity signals. These high-intensity plaques (HIPs) are quantitatively assessed using the plaque-to-myocardium signal intensity ratio (PMR). Our goal is to assess the effect of EPA/DHA on coronary HIPs detected with T1WI in patients with CAD on statin treatment.

**Methods/design:**

This prospective, controlled, randomized, open-label study examines the effect of 12 months of EPA/DHA therapy and statin treatment on PMR of HIPs detected with CMR and computed tomography angiography (CTA) in patients with CAD. The primary endpoint is the change in PMR after EPA/DHA treatment. Secondary endpoints include changes in Hounsfield units, plaque volume, vessel area, and plaque area measured using CTA. Subjects are randomly assigned to either of three groups: the 2 g/day EPA/DHA group, the 4 g/day EPA/DHA group, or the no-treatment group.

**Discussion:**

This trial will help assess whether EPA/DHA has an anti-atherosclerotic effect using PMR of HIPs detected by CMR. The trial outcomes will provide novel insights into the effect of EPA/DHA on high-risk coronary plaques and may provide new strategies for lowering the residual risk in patients with CAD on statin therapy.

**Trial registration:**

The University Hospital Medical Information Network (UMIN) Clinical Trials Registry, ID: UMIN000015316. Registered on 2 October 2014.

**Electronic supplementary material:**

The online version of this article (doi:10.1186/s13063-017-2353-1) contains supplementary material, which is available to authorized users.

## Background

Evidence strongly suggests that lowering low-density lipoprotein (LDL)-cholesterol levels with statins reduces the risk of cardiovascular disease as primary and secondary prevention of atherosclerotic cardiovascular events [1–7]. However, many clinical trials have found a significant residual risk for cardiovascular events even in the setting of optimal LDL-cholesterol reduction with statins [8, 9]. Thus, there is a need to establish strategies beyond lowering LDL-cholesterol levels with statins to reduce the risk of cardiovascular events.

Epidemiologic studies have shown that increasing the intake of long-chain n-3 polyunsaturated fatty acids (n-3 PUFAs), especially eicosapentaenoic acid (EPA) and docosahexaenoic acid (DHA), is inversely associated with cardiovascular or cerebrovascular disease incidence [10–15]. The LC n-3 PUFAs have a different anti-atherosclerotic mechanism from statins, including triglyceride and remnant lipoprotein-lowering effects [16]. In experimental study, EPA/DHA treatments significantly attenuated the development and destabilization of atherosclerotic plaques [17]. Although meta-analysis failed to demonstrate the inhibitory effect of cardiovascular events by LC n-3 PUFA supplementation, the effects of high-dose LC n-3 PUFAs on cardiovascular outcome should be discussed (most previous and on-going studies use 1 g EPA/DHA) [18]. Indeed, higher-dose EPA (1.8 g) could reduce the residual risk of cardiovascular diseases in patients receiving LDL lowering with statins [19]. And previous human studies have investigated the effect of high-dose EPA on plaque stability or plaque composition [20, 21]. Therefore, the present study focuses on the effects of high-dose administration of EPA/DHA on coronary plaques.

We have reported that coronary high-intensity plaques (HIPs) detected with non-contrast T1-weighted imaging (T1WI) on cardiac magnetic resonance (CMR) are associated with computed tomography angiography (CTA) – and intravascular ultrasound-derived – features of high-risk plaques [22, 23]. HIPs, which can be uniquely assessed using the plaque-to-myocardium signal intensity ratio (PMR), [22] are significantly associated with future coronary events [24]. More recently, in the AQUAMARINE (Attempts at Plaque Vulnerability Quantification with Magnetic Resonance Imaging Using Non-contrast T1-weighted Technic) study, we have demonstrated that intensive lipid-lowering therapy with pitavastatin reduces the PMR of coronary HIPs by approximately 25% [25]. Thus, non-contrast T1WI is now being established as a less-invasive technique for evaluating high-risk coronary plaques, and as such, might be a promising predictive factor in patients at high risk.

The present AQUAMARINE-EPA/DHA study is designed to assess the anti-atherogenic effect of EPA/DHA in an exploratory manner. We will study the change in PMR of coronary HIPs detected using CMR after 12 months of EPA/DHA therapy.

## Methods/design

### Aim

The aim of this study is to assess the effect of EPA/DHA on PMR of HIPs in patients with coronary artery disease (CAD) detected using non-contrast T1WI imaging with CMR.

### Study design

This is a single-center, triple-arm, parallel-group, randomized controlled, open-label, superiority trial examining the effect of 12 months of EPA/DHA therapy on coronary HIPs in patients with CAD between May 2014 and April 2018. Eligible subjects are randomly assigned to the 2 g/day EPA/DHA group, the 4 g/day EPA/DHA group, or the no-treatment group (allocation rate 1:1:1). The randomization stratified on following variables (age, gender, presence or absence of type 2 diabetes mellitus, and PMR of the primary coronary lesion measured with non-contrast T1WI) (Fig. 1).

**Fig. 1 Fig1:**
[figure not shown]
Study flow of this study

### Patient eligibility and recruitment

Patients aged 20 years or older with proven or suspected CAD receiving statin therapy are eligible for the study. It is necessary for eligible subjects to achieve an optimal LDL-cholesterol level (LDL-cholesterol < 100 mg/dl) recommended by the Japan Atherosclerosis Society. Patients are excluded if they are scheduled for percutaneous coronary intervention (PCI) or coronary artery bypass grafting (CABG) or had taken EPA/DHA within 12 weeks before providing informed consent, type 1 diabetes mellitus or type 2 diabetes mellitus with uncontrolled hyperglycemia (glycosylated hemoglobin (HbA1C) ≥ 8.0%), or the presence of bleeding (e.g., hemophilia, capillary fragility, gastrointestinal tract ulceration, urinary tract bleeding, hemoptysis, vitreous hemorrhage).

### Study procedures

Eligible patients are randomly assigned to the 2 g/day EPA/DHA group, the 4 g/day EPA/DHA group, or the no-treatment group. Prospective, serial, non-contrast T1WI and CTA examinations are performed at baseline and after 12 months of EPA/DHA treatment (Fig. 2).

**Fig. 2 Fig2:**
[figure not shown]
Example template of recommended content for the schedule of enrollment, interventions, and assessments

#### Inclusion and exclusion criteria

##### Inclusion criteria

Subjects must meet all of the following criteria:Be aged 20 years or olderDiagnosed with dyslipidemia and have received instructions for a 3–6-month lifestyle modificationDiagnosed with coronary artery disease with > 25% coronary stenosis measured by CTA or invasive coronary angiography (CAG)On statin therapy at a fixed dose and administration method for at least 4 weeks before providing informed consentHave at least one coronary plaque with PMR ≥ 1.0 with non-contrast T1WI on the screening examinationSerum LDL-cholesterol level < 100 mg/dL on the screening testCapable of visiting the study centers on an outpatient basisCapable of providing written consent before study participation

##### Exclusion criteria

Those who meet any of the following criteria are ineligible for the study:Use of LC n-3 PUFA preparations within 12 weeks before providing informed consentScheduled to undergo PCI or CABG during the observation periodPresence of type 1 diabetes mellitus or type 2 diabetes mellitus, with uncontrolled hyperglycemia (HbA1C ≥ 8.0%)Clinically apparent impairment of renal function (estimated glomerular filtration rate < 40 ml/min)Presence of bleeding (e.g., hemophilia, capillary fragility, gastrointestinal tract ulceration, urinary tract bleeding, hemoptysis, vitreous hemorrhage)History of hypersensitivity to any component of the investigational productPregnancy, possible pregnancy, or nursing

### Outcomes

#### Primary endpoint

The primary endpoint is the change in PMR of the primary coronary lesion measured by non-contrast, T1-weighted cardiac imaging from baseline to study completion or discontinuation (Table 1).

**Table 1 Tab1:** Summary of the study outcome and measures

Primary endpoint
Change in PMR in the primary lesion measured by CMR imaging
Secondary endpoint
Change in PMR in all lesions measured by CMR imaging Percentage change in PMR in the primary lesion measured by CMR imaging Percentage change in PMR in all lesion measured by CMR imaging Changes in Hounsfield units, plaque volume, vessel area, and plaque area in the primary lesion measured by CTA Changes in Hounsfield units, plaque volume, vessel area, and plaque area in all lesions measured by CTA Percentage changes in Hounsfield units, plaque volume, vessel area, and plaque area in the primary lesion measured by CTA Percentage changes in Hounsfield units, plaque volume, vessel area, and plaque area in all lesions measured by CTA
Other endpoint
Changes and percentage changes in triglycerides, total cholesterol, LDL-cholesterol, HDL-cholesterol, non-HDL-cholesterol, VLDL-cholesterol, remnant-like cholesterol, LPL activity, and high-sensitivity C-reactive protein Changes and percentage changes in small, dense LDL and mean LDL particle diameter Changes and percentage changes in EPA, DHA, AA, EPA/AA ratio, and omega-3 index (weight percentage of eicosapentaenoic acid [EPA, C20:5ω3] and docosahexaenoic acid [DHA, C20:6ω3] in total fatty acids out of all lipids) Changes and percentage changes in leptin and adiponectin

*AA* arachidonic acid, *CMR* cardiac magnetic resonance, *CTA* computed tomography angiography, *HDL* high-density lipoprotein, *LDL* low-density lipoprotein, *LPL* lipoprotein lipase, *PMR* plaque-to-myocardium signal intensity ratio, *VLDL* very-low density lipoprotein

#### Secondary endpoint

Change in PMR in all lesions measured by non-contrast, T1-weighted CMR imaging from baseline to study completion or discontinuationPercentage change in PMR of the primary lesion measured by non-contrast, T1-weighted CMR imaging from baseline to study completion or discontinuationPercentage change in PMR of all lesions measured by non-contrast, T1-weighted CMR imaging from baseline to study completion or discontinuationChange and percentage change in Hounsfield units, plaque volume, vessel area, and plaque area of the primary lesion measured by CTA from baseline to study completion or discontinuationChange and percentage change in Hounsfield units, plaque volume, vessel area, and plaque area of all lesions measured by CTA from baseline to study completion or discontinuation

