#### Sample size

Based on the result from our previous study, a clinically meaningful change from baseline in PMR was assumed to be − 0.15 in both the 2 g/day and the 4 g/day LC n-3 PUFA groups, and no change in the no-treatment group, with a common standard deviation of 0.2 among the groups. The sample size per group of 46 archives 90% power to detect the assumed difference in changes, using a two-group, one-sided *t* test of 1.25% significance level, where the overall significance level of the one-sided test for the two comparisons (i.e., the 2 g/day group versus the no-treatment group, and the 4 g/day LC n-3 PUFA group versus the no-treatment group) was 2.5% and the Bonferroni adjustment was applied to control the Type I error rate. Allowing for adjustment of withdrawals, missing data or loss to follow-up, 50 subjects per group will be recruited into the trial.

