#### Statistical methods

All the analysis will be made on an intent-to-treat (ITT) basis. The 2 g/day and the 4 g/day EPA/DHA groups will be compared against the no-treatment group for all primary analysis. For the primary outcome, treatment effects between the groups and their 95% confidence intervals are calculated from analysis of covariance (ANCOVA) models with adjustment for baseline values of the outcome measure. To confirm the conclusion from ITT-based analysis, the same analysis is repeated on a per-protocol set (PPS), where criteria for determining the PPS assignment would be established and confirmed by the Steering Committee. For secondary and other outcomes, we will use the chi-squared test for binary outcomes, and a *t* test for continuous outcomes. For subgroup analyses, we will use regression methods with appropriate interaction terms (respective subgroup × treatment group). Multivariable analyses will be based on logistic regression for binary outcomes and linear regression for continuous outcomes. We will examine the residual to assess model assumptions and goodness-of-fit.

All *p* values will be reported to four decimal places with *p* values less than 0.001 reported as *p* < 0.001. Up-to-date versions of SAS (SAS Institute, Cary, NC, USA) will be used to conduct analyses. For all tests, we will use two-sided *p* values with an alpha ≤ 0.05 level of significance

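### The ten 'all lesions' secondary measures are assigned a t test with no stated unit of analysis; if lesions are pooled as independent observations, the false-positive rate exceeds 5%

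*Protocol article*

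**What the plan says.** All references are to the protocol article.

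- **Primary endpoint.** One lesion per patient: "The primary endpoint is the change in PMR of the primary coronary lesion". No clustering arises.
- **Secondary endpoint.** The list opens with "Change in PMR in all lesions measured by non-contrast, T1-weighted CMR imaging". It later adds four CTA measures, each as an absolute and as a percentage change; for the last of the four the text reads: "plaque area of all lesions measured by CTA from baseline to study completion or discontinuation".
- **Inclusion criteria.** A patient needs one or more plaques with a PMR of 1.0 or higher, so some patients may have several.
- **Study design and Randomization.** Subjects are allocated, not lesions.
- **Statistical methods.** "For secondary and other outcomes, we will use the chi-squared test for binary outcomes, and a *t* test for continuous outcomes". On the level: "For all tests, we will use two-sided *p* values with an alpha ≤ 0.05 level of significance". The only other model that could apply to these outcomes is in this sentence: "Multivariable analyses will be based on logistic regression for binary outcomes and linear regression for continuous outcomes".

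The article does not say whether an all-lesions measure enters the t test lesion by lesion or as one summary per patient. It mentions no patient-level mean or total, mixed model, generalised estimating equation or cluster-robust variance.

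**The concern.** A two-sample t test assumes independent observations. Lesions in one patient share the assigned treatment, the statin regimen, the lipid levels and the scan sessions, so their changes are likely to be positively correlated. If each lesion is entered as an observation, the standard error is too small, the interval too narrow and the p value too low.

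The distinction between the primary lesion and all lesions has meaning only if some patients have more than one. If every patient had one lesion, the all-lesions measures would duplicate the primary-lesion measures.

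At stake is how the secondary results are read. More than half of the secondary measures could show nominal significance too often, and could appear to support the treatment beside a null primary result. The trial is open-label, although the image readers are blinded, so the unit of analysis should be fixed before the data are seen.

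**Working it through.** **1. Count of measures affected (Secondary endpoint).**
- PMR: change in all lesions, percentage change in the primary lesion, percentage change in all lesions = 3, of which 2 are all-lesions.
- CTA: 4 measures × 2 (change, percentage change) × 2 (primary lesion, all lesions) = 16, of which 8 are all-lesions.
- Total 3 + 16 = 19, of which 2 + 8 = 10 are all-lesions.

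**2. The plan's own figure.** The Sample size section states that "a clinically meaningful change from baseline in PMR was assumed to be − 0.15 in both the 2 g/day and the 4 g/day" groups, against no change without treatment. It uses SD 0.2, a one-sided 1.25% test and 90% power.
- Normal approximation: n = 2 × (2.241 + 1.282)² × 0.2² / 0.15² = 44.1, so 45 per group.
- Noncentral t: power is 89.7% at 45 and 90.4% at 46.
- The stated 46 is reproduced. Recruiting 50 allows for 8% loss (46 / 0.92 = 50).

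This calculation concerns one lesion per patient and is untouched by what follows.

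**3. Actual error of a t test on pooled lesions.** Let m be lesions per patient and ICC the within-patient correlation of the analysed change. Both are assumptions.
- Design effect: DE = 1 + (m − 1) × ICC.
- Actual two-sided error at nominal 5%: 2 × [1 − Φ(1.96 / √DE)].
- Example, m = 2 and ICC = 0.3: DE = 1.3, √DE = 1.140, 1.96 / 1.140 = 1.719, error 8.6%.

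| m | ICC 0.1 | ICC 0.3 | ICC 0.5 |
|---|---|---|---|
| 1.5 | 5.6% | 6.8% | 8.0% |
| 2 | 6.2% | 8.6% | 11.0% |
| 3 | 7.4% | 12.1% | 16.6% |

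With m = 1 or ICC = 0, DE = 1 and the error is 5.0%.

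**4. Simulation check.** 50 patients per arm, no treatment effect, 8,000 runs per setting.

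| Lesions per patient | ICC | t test on pooled lesions | t test on patient means |
|---|---|---|---|
| 2 | 0.3 | 8.9% | 5.2% |
| 2 | 0.5 | 10.7% | 4.5% |
| 3 | 0.3 | 12.0% | 5.1% |
| 3 | 0.5 | 16.6% | 5.1% |
| 1, 2 or 3 (50/30/20%) | 0.3 | 8.6% | 4.9% |
| 1, 2 or 3 (50/30/20%) | 0.5 | 11.1% | 5.0% |

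The simulation agrees with the formula for equal counts. When counts vary, using the mean for m understates the inflation. The 50/30/20% mix has a mean of 1.7, and the value to use for m is Σk²/Σk = (0.5 + 1.2 + 1.8) / 1.7 = 2.06. That gives DE = 1.32 and an error of 8.8% at ICC 0.3, close to the simulated 8.6%.

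**5. Effect on interval width.** A pooled-lesion interval is too narrow by a factor of √DE. Over the table in step 3 this runs from √1.05 = 1.02 to √2.0 = 1.41.

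**The case against.** A reader might infer that the plan treats correlated lesions as independent, or that the t test is itself the wrong test. The article supports neither. The endpoint section says what is measured, not what counts as an observation. Subjects are randomised, the sample size is per subject, and the comparisons are between treatment groups under intention to treat. A t test on each patient's mean or total fits the text and, by step 4, holds its level. That part of the objection stands, so the point is conditional on lesions being the unit.

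It can also be said that the rule for combining lesions is a detail an article leaves to the full protocol or analysis plan. This has some force. However, the article does not leave the analysis open: it assigns one test to every continuous secondary outcome, whether it rests on one lesion or several. The same text therefore permits a valid and an invalid analysis. Checking residuals, which the section also plans, is not tied to within-patient correlation and carries no stated remedy.

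Three limits also stand. The lesion counts and the ICC are not in the article, so no single inflation figure can be given, and it is slight at the low end. The article does not say how the myocardial reference signal is sampled, so a shared PMR denominator cannot be assumed. Only secondary endpoints are involved, in a study that describes its aim as exploratory.

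**Conclusion.** The concern holds in conditional form. Ten secondary measures are assigned a t test with neither a unit of analysis nor any handling of within-patient correlation. If lesions are pooled, the nominal 5% test has an actual error of about 5.6% to 16.6%, assuming a mean of 1.5 to 3 lesions per patient and an ICC of 0.1 to 0.5. If one value per patient is tested, the error stays at about 5% (4.5% to 5.2% in simulation).

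Nothing here bears on the validity of the primary endpoint, which uses one lesion per patient, or on the stated 46 per group, which is reproduced. The point is worth correcting because the choice is easily settled now and would be open to question after the data are seen.

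**What to change.** In Statistical methods, name the patient as the unit of analysis for every all-lesions endpoint, and specify one of these:

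- **Patient-level analysis.** Average the measure over each patient's lesions and compare each dose group with no treatment by ANCOVA, adjusted for the patient's mean baseline value. This follows the method already planned for the primary outcome.
- **Lesion-level analysis.** Fit a linear mixed model with treatment, the lesion's baseline value and a random patient intercept.

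One of the two should be chosen in advance, because they weight patients with many lesions differently. Keeping the planned t test on one value per patient would also remove the false-positive problem, but without the baseline adjustment used for the primary outcome.

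The cost is a change of analysis wording. Recruitment, imaging and data collection stay as they are. Intervals will be wider than a pooled-lesion test would give, by roughly 2% to 41% under the assumptions above, and that width is the correct one.

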#### Other variables

Change and percentage change in triglycerides, total cholesterol, LDL-cholesterol, high-density lipoprotein (HDL)-cholesterol, non-HDL-cholesterol, very-low-density lipoprotein (VLDL)-cholesterol, remnant-like lipoprotein cholesterol, lipoprotein lipase (LPL) activity, and high-sensitivity C-reactive protein from baseline to study completion or discontinuationChange and percentage change in small, dense LDL and mean LDL particle diameter from baseline to study completion or discontinuation (LDL diameter is measured using Lipoprint^TM^ system (Quantimetrix))Change and percentage change in EPA, DHA, arachidonic acid (AA), EPA/AA ratio, and LC n-3 PUFA (percentage of EPA [C20:5ω3] and DHA [C22:6ω3] by weight in all fatty acids out of all lipids) from baseline to study completion or discontinuationChange and percentage change in leptin and adiponectin from baseline to study completion or discontinuation

#### Sample size

Based on the result from our previous study, a clinically meaningful change from baseline in PMR was assumed to be − 0.15 in both the 2 g/day and the 4 g/day LC n-3 PUFA groups, and no change in the no-treatment group, with a common standard deviation of 0.2 among the groups. The sample size per group of 46 archives 90% power to detect the assumed difference in changes, using a two-group, one-sided *t* test of 1.25% significance level, where the overall significance level of the one-sided test for the two comparisons (i.e., the 2 g/day group versus the no-treatment group, and the 4 g/day LC n-3 PUFA group versus the no-treatment group) was 2.5% and the Bonferroni adjustment was applied to control the Type I error rate. Allowing for adjustment of withdrawals, missing data or loss to follow-up, 50 subjects per group will be recruited into the trial.

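### The two dose comparisons need one multiplicity rule in the analysis section; Holm would keep the 2.5% familywise limit and give more power than the Bonferroni split used for sizing

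*Protocol article*

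**What the plan says.** The Sample size section of the protocol article bases the trial on two comparisons, each dose against no treatment. The change in PMR "was assumed to be − 0.15 in both the 2 g/day and the 4 g/day LC n-3 PUFA groups", with "no change in the no-treatment group" and a "common standard deviation of 0.2 among the groups". Each comparison is a one-sided two-group t test at 1.25%. The overall one-sided level for the pair is 2.5%, and "the Bonferroni adjustment was applied to control the Type I error rate". On this basis, "The sample size per group of 46 archives 90% power to detect the assumed difference in changes", and 50 per group are to be recruited to allow for losses. No step-down or ordered procedure is mentioned.

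The Statistical methods section repeats the two primary comparisons, now by ANCOVA adjusted for baseline with 95% confidence intervals. It names no multiplicity adjustment and applies a two-sided significance level of 0.05 to all tests.

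**The concern.** There are two linked issues.

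- **Which rule governs.** The familywise limit appears only in the sample size calculation. The section that says how the data will be tested does not carry it over. Read literally, that section tests each dose at two-sided 0.05, which is one-sided 2.5% in the favourable direction, without adjustment.
- **Whether the sizing rule is the best one to carry over.** Single-step Bonferroni holds the second dose to 1.25% even after the first has succeeded, although the 2.5% familywise limit does not require this. The loss is largest when both doses work, and that is the scenario the plan assumes: a change of −0.15 "in both the 2 g/day and the 4 g/day LC n-3 PUFA groups, and no change in the no-treatment group".

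At stake are a few points of power per dose, rather more for showing both doses, and clarity about which error rate the primary analysis controls.

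**Working it through.** **Inputs, all from the Sample size section unless noted.** Difference 0.15 for each dose against no treatment; SD 0.2; n = 46 per group; familywise limit one-sided 2.5%; Bonferroni level one-sided 1.25% per comparison. Allocation is 1:1:1 (Study design section), so both comparisons share one control arm of the same size.

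**Step 1: reproduce the plan's figure.**
- Standard error of a difference: 0.2 × √(2/46) = 0.0417.
- Noncentrality: 0.15 / 0.0417 = 3.597, with 2 × 46 − 2 = 90 degrees of freedom.
- One-sided critical value at 1.25%: t = 2.280.
- Power by the noncentral t distribution: 90.4%. With 45 per group it is 89.7%.

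The stated 46 is therefore the smallest n that reaches 90% per comparison. The plan's figure is right.

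**Step 2: define the two procedures.** One-sided p values, familywise limit 2.5%.
- Bonferroni: a dose is declared effective if its p value is at most 0.0125.
- Holm: the smaller p value is tested at 0.0125. If it is significant, the larger is tested at 0.025.

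Holm rejects whatever Bonferroni rejects. It controls the familywise error under any dependence, including that from the shared control arm.

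**Step 3: simulate the three-arm trial.** Two million replicates with a shared control and pairwise t tests, both true effects equal to 0.15.

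| | Bonferroni | Holm |
|---|---|---|
| n = 46: power per dose | 90.4% | 93.5% |
| n = 46: both doses shown | 83.9% | 90.0% |
| n = 46: at least one dose shown | 97.0% | 97.0% |
| n = 50: power per dose | 92.8% | 95.3% |
| n = 50: both doses shown | 87.6% | 92.7% |

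Check: the two doses have equal effects, so power per dose is the average of power for at least one and power for both. For Holm at 46 this is (97.0 + 90.0)/2 = 93.5. For Bonferroni it is (97.0 + 83.9)/2 = 90.45, which agrees with 90.4 within rounding.

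Under Holm, about 41 per group would give the 90% per dose (90.3%) that needs 46 under Bonferroni.

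**Step 4: error rates at 46 per group.**
- Neither dose works: the chance of at least one false positive is 2.3% under both procedures.
- Only one dose works (effect 0.15): the false-positive rate for the other is about 1.25% with Bonferroni and 2.5% with Holm. Both are within the limit. Power for the effective dose is 90.4% either way.
- Each dose tested at one-sided 2.5% without adjustment, as the Statistical methods section reads literally: the chance of at least one false positive when neither works is about 4.5%, above the 2.5% limit in the Sample size section.

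**The case against.** The strongest case against raising this is that nothing here is wrong. Bonferroni is a valid method, the sample size reproduces, and the stated target of 90% per comparison is met. A design sized with Bonferroni can still be tested with Holm, and the exact decision rule may sit in a SAP that is not shown. The Background section also calls the study exploratory. All of this stands, and it is why the point is an optional improvement.

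A reader might infer three stronger things that the document does not support.

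- **That the trial is certain to lose power.** The Bonferroni rule appears only in the Sample size section. The literal wording of Statistical methods is more liberal than either procedure, and Holm would be stricter than that wording. The loss arises only if the sizing rule governs the analysis.
- **That Holm costs nothing.** It costs nothing in familywise level or sample size. But Bonferroni gives more protection against a false claim for an ineffective dose when the other dose works, and it has simple matching 97.5% intervals, which Holm lacks. The plan states 95% intervals, so it does not now use that advantage.
- **That the chance of a positive trial rises.** Power for at least one dose is the same under both, and showing both doses is not a target that the plan sets.

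The power figures come from unadjusted t tests. The planned ANCOVA would raise power under either procedure if baseline PMR predicts the change, and the absolute gain would then be smaller.

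**Conclusion.** The point holds as a low-priority improvement. The choice of Bonferroni and the sample size of 46 are both sound. What should be settled is that the familywise rule used for sizing is absent from the analysis section, and that Holm is the more efficient way to write it there.

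The gain over Bonferroni at 46 per group is about 3 percentage points per dose and about 6 for both doses, at the same 2.5% limit. Put another way, if both doses work, the chance of failing to show at least one of them falls from about 16% to 10%. The result rests on the plan's own assumptions: equal effects of 0.15, SD 0.2, equal arms and 46 evaluable per group. If only one dose works, Holm adds essentially nothing for that dose.

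**What to change.** In the Statistical methods section, state one rule for the two primary ANCOVA comparisons and exempt them from the general two-sided 0.05 statement. Suggested wording: *The two comparisons of each dose with no treatment will be tested by Holm's procedure at a familywise one-sided 2.5%. The smaller p value is tested at one-sided 0.0125; if it is significant, the larger is tested at one-sided 0.025.* If two-sided p values are reported, these thresholds correspond to 0.025 and 0.05 with the difference in the favourable direction.

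Keep 46 evaluable and 50 recruited per group; the stated 90% per comparison then becomes conservative. Report 97.5% intervals for both effects, with a note that the interval for the second dose may not match the step-down decision. Make the change before any results by treatment group are known.

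The cost is a sentence or two in the analysis section and the SAP, plus the two trade-offs already described: less protection for an ineffective dose when the other works, and the loss of exactly matching intervals. If the sponsor values those more than the added power, keeping Bonferroni is acceptable, but the rule must still be written into the Statistical methods section.
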